### Patient follow-up

The follow-up will include seven regular visits for check-up every three to six months with a total of 24 month after discharge. Further follow-up will be conducted as quarterly phone calls to determine survival up to 60 months after discharge. For a detailed listing of the procedures and items recorded in the eCRF for each trial visit, see Table 1. If a tumor recurrence is clinically suspected during the follow-up period, a CT of the thorax and abdomen as well as an endoscopy will be performed on indication to further document the disease-free survival. Loss-to-follow-up will be minimised by commissioning a person at the trial site to manage and encourage follow-up and providing of excellent and free medical care. We therefore assume a small attrition rate of 0.05 per year and study arm.

V0 Screening, V1 Baseline/Randomization, V2 Discharge, V3 + 1 month, V4 + 3 months, V5 + 6 months, V6 + 9 months, V7 + 12 months, V8 + 18 months, V9 + 24 months, Survival Follow-up up to 60 months – quarterly by phone. ^1^Negative serum pregnancy test during screening period for women of child-bearing age. ^2^Only in case of a clinically suspected tumor recurrence.

**Table 1 Tab1:** Visit schedule

	**V0**	**V1**	**V2**	**V3**	**V4**	**V5**	**V6**	**V7**	**V8**	**V9**	**Survival-** **Follow-up**
Demography	X										
Medical history	X										
Oncological history	X										
Tumor classification	X										
Pregnancy test^1^		X									
Inclusion / Exclusion		X									
Laboratory	X										
Biopsy	X										
Randomisation		X									
Physical examination	X		X	X	X	X	X	X	X	X	
Anamnesis	X			X	X	X	X	X	X	X	
Endoscopy	X				X^2^	X^2^	X^2^	X^2^	X^2^	X^2^	
CT/MRI	X				X^2^	X^2^	X^2^	X^2^	X^2^	X^2^	
Concomitant Medication	X		X	X	X	X	X	X	X	X	
EORTC QLQ-C30, −STO22, −OG 25-		X	X		X	X	X	X	X	X	
OP – Description			X								
Post-OP Complication			X								
Pathology			X								
Reference pathology			X								
AE/SAE			X	X	X						
Survival				X	X	X	X	X	X	X	X
EOS											or earlier for premature withdrawal

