### Outcome measures

The primary endpoint is overall survival, which will be followed up until 60 months after discharge of surgery. The key secondary endpoints are complete resection (R0), post-operative complications according to the Esophageal Complications Consensus Group (ECCG) definitions [18] and scored on severity by the the Clavien-Dindo classification [19], number and localization of tumor infiltrated lymph nodes at dissection, disease-free survival, quality of life (EORTC QLQ-C30, QLQ-STO22, and QLQ-OG25 after 3, 6, 9, 12, 18, 24 months) and cost-effectiveness.

After consolidation of the EORTC questionnaires data during the course of the trail, a cost effectiveness analysis of both procedures based on direct costs and resulting QALYs will be performed and the incremental cost-effectiveness ratio will be calculated. For simplification of the process, only German sites classified as excellence centers will be included into the analysis, so that consistent national costs (e.g. DRG based, medical supply, labor costs based on tariffs) can be comparable.

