### Statistical analysis

The primary analysis will be performed on the full analysis set (intention-to-treat) and comprises all patients with written informed consent and who were operated. The analysis is as assigned by stratified randomization (i.e. site or surgeon and tumor stage). The primary outcome of overall survival will be evaluated by the stratified log-rank test and is event-driven (i.e. following observation of 188 events). The hazard ratio with 95% confidence interval (CI) is estimated by stratified Cox regression. The assumption of non-informative censoring is examined using standard approaches (i.e. Kaplan-Meier curves, examining patterns of censoring across covariates and association between censoring and covariates). The key secondary outcome R0 resection rate is analyzed by comparing the corresponding odds between treatment groups with the stratified Mantel-Haenszel test. A missing assessment is counted as failure. Contingency tables of strata with “empty rows or columns” are pooled. The combined Mantel-Haenszel odds ratio with 95% CI is calculated. The potential impact of clustering associated with both interventions is addressed in a sensitivity analysis [22, 23]. The secondary outcome quality of life is averaged over 36 months (area under curve, AUC) and tested for non-inferiority of the esophagectomy arm regarding a margin of 80%. Missing values are linearly interpolated. The key outcomes overall survival, R0 resection and quality of life are tested in a fixed sequence, thus no alpha-correction is required for strong type I error control (5%, two-sided).

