Subgroup analyses are done by sex, tumor stage and (essential) compliance with the protocol (i.e. per protocol analysis). Adverse events are summarized and listed by seriousness, severity and relatedness to treatment. Cumulative survival 30, 36 and 60 months following surgery is estimated by Kaplan-Meier method (with 95% CI according to Greenwood’s formula). Methods for rates and proportions are used to describe hospital mortality and the incidence of post-operative complications. A linear mixed model is fit to health related quality of life data from EORTC questionnaires QLQ-C30, QLQ-STO22, and QLQ-OG25. Cost-effectiveness is determined as the ratio ∆C/∆E where ∆C is the difference in resource use (costs) and ∆E the gain in months of life or in quality of life. The cost-effectiveness (cost per life-month gained or cost per quality-of-life-unit) will be calculated from a societal perspective.

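### The confirmatory quality-of-life test is described without the baseline score or the randomization strata, which gives up precision that could be had at no cost

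*Protocol article*

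**What the plan says.** In the visit schedule (Patient follow-up, Table 1), the row "EORTC QLQ-C30, −STO22, −OG 25" has its first mark under V1, then marks under V2 and V4 to V9. The legend defines the early visits: "V0 Screening, V1 Baseline/Randomization, V2 Discharge". A pre-operative score is therefore planned for every randomized patient.

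Outcome measures lists the times of the quality-of-life endpoint: "QLQ-OG25 after 3, 6, 9, 12, 18, 24 months". V1 is not among them.

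Statistical analysis describes the test: "The secondary outcome quality of life is averaged over 36 months (area under curve, AUC) and tested for non-inferiority of the esophagectomy arm". The section puts the margin at 80% and does not say on which scale. It adds a missing-data rule: "Missing values are linearly interpolated". No baseline value, covariate or stratum is named for this test. In the same section, overall survival has a stratified log-rank test and a stratified Cox model, and R0 has a stratified Mantel-Haenszel test. Quality of life comes last of the three in the fixed testing sequence.

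A separate sentence covers a further analysis: "A linear mixed model is fit to health related quality of life data from EORTC questionnaires". It lists neither covariates nor response visits.

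**The concern.** Quality of life is a confirmatory outcome here, and the test is one of non-inferiority, so success depends on how narrow the confidence interval is. The article's Background and Discussion cite retrospective studies in which quality of life was better after gastrectomy. Esophagectomy must therefore be shown non-inferior where earlier data point the other way. Power is given for survival and R0 but not for this test, and deaths will thin the questionnaires.

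In that setting, a pre-operative score that predicts the later scores is worth using. If it is left out, the variation it explains stays in the error term, and a chance difference between arms at baseline carries over in part to the comparison against the margin. This remains true whichever averaging period or interpolation rule is finally used.

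**Working it through.** The plan states no sample size, power or SD for quality of life, so there is no figure of its own to reproduce.

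**Inputs from the article.** Total N is 262 (Sample size calculation). Assumed survival at 2.5 years is 45% after esophagectomy and 30% after gastrectomy (same section).

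**Assumptions, not in the article.** Allocation is 1:1, giving 131 per arm. The correlation r between the V1 score and the post-operative AUC average is 0.2 to 0.6. The SD is 20 points, the same for both.

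**Step 1: precision.** ANCOVA on baseline multiplies the variance of the arm contrast by 1 − r². The equivalent total sample for an unadjusted test is 262/(1 − r²). For illustration, take an unadjusted test with exactly 80% power at two-sided 5%. Adjusted power is then Φ[(1.96 + 0.84)/√(1 − r²) − 1.96].

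| r | 1 − r² | Variance cut | Equivalent N | Power, from 80% |
|---|---|---|---|---|
| 0.2 | 0.96 | 4% | 273 | 81.6% |
| 0.3 | 0.91 | 9% | 288 | 83.6% |
| 0.4 | 0.84 | 16% | 312 | 86.4% |
| 0.5 | 0.75 | 25% | 349 | 89.9% |
| 0.6 | 0.64 | 36% | 409 | 93.8% |

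**Step 2: chance imbalance.** The standard error of the baseline difference is 20 × √(2/131) = 2.47 points. A gap of 5 points is 5/2.47 = 2.02 standard errors, so a gap at least that large in either direction has a probability of about 4%.

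**Step 3: carry-over.** With equal SDs, a baseline gap moves the expected unadjusted follow-up contrast by r times the gap. For 5 points this is 0.2 × 5 = 1 point up to 0.6 × 5 = 3 points.

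**Step 4: V1 as a point on the AUC.** Because V2 is also a questionnaire visit, V1 would carry a trapezoid weight of half the V1 to V2 interval. If that interval is 1 to 2 months (assumed), the weight in a 36-month average is 0.5/36 = 1.4% to 1/36 = 2.8%. Counting V1 in the AUC thus adds little noise, but it also does not bring the gain in Step 1.

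**Step 5: thinning by death.** Under exponential survival, the proportion alive at 24 months is 0.45^(24/30) = 53% and 0.30^(24/30) = 38%. That is about 69 and 50 of 131. Late questionnaires will come from far fewer than 262 patients.

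**The case against.** The strongest objection is that the article is silent and does not exclude anything. It is a condensed report, a full protocol exists, and covariate lists are often left to it or to the SAP. In addition, the stated primary analysis follows the stratified randomization, and that might be meant to extend to quality of life.

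For the mixed model this objection succeeds. A reader might infer that baseline is missing from that model too, but the documents do not show it. The model is fitted to the questionnaire data, which by Table 1 include V1, and V1 could enter as a covariate or as a response.

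For the confirmatory AUC test it succeeds only in part. That test is described down to its interpolation rule, the endpoint times omit V1, and the neighbouring tests are explicitly stratified. As written it is an unadjusted comparison, and the undisclosed full documents may already improve on it.

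It is also fair that the benefit rests wholly on an assumed correlation. Patients given FLOT complete V1 after four preoperative cycles, and nothing in the article supports a value as high as 0.6. At 0.2 to 0.3 the gain is small. Finally, the test is reached only if survival and R0 both succeed.

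**Conclusion.** The point holds as an available improvement of minor weight. The stated quality-of-life test makes no declared use of a baseline score already being collected, nor of the randomization strata. The variance cut is 4% to 36% for an assumed correlation of 0.2 to 0.6, and no narrower figure can be derived from the documents.

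Three stronger readings are not supported:

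- **That the test is biased or invalid.** Randomization protects the unadjusted comparison and its type I error. The loss is one of efficiency.
- **That a chance baseline gap passes straight into the result.** It is scaled by the correlation, so 5 points becomes about 1 to 3.
- **That gaps of that size are common.** Under the assumed SD and arm size, the chance is about 4%.

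No stated sample size, event number or significance level is affected. The 36-month averaging period against questionnaires that end at 24 months is a separate matter.

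**What to change.** Specify that the post-operative quality-of-life AUC is compared between arms by ANCOVA. The V1 score and the randomization tumor stage should be covariates, with site or surgeon added where the number of patients per level allows. Start the AUC at the first post-operative questionnaire, so that V1 acts as a covariate and not also as part of the outcome. Base the non-inferiority confidence interval on the adjusted contrast, on whichever scale the 80% margin is defined, and state that scale in the same sentence. Fix the covariates before any comparison by arm.

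The mixed model needs no correction on this ground. A line saying how V1 enters it would remove the doubt.

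The cost is wording in the SAP. No further data, patients or significance level are needed, because the V1 questionnaire is already scheduled.

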### Sample size calculation

The primary endpoint is overall survival. We assume a cumulative survival after 2.5 years of 45% for transthoracic esophagectomy and 30% for transhiatal extended gastrectomy (see Fig. 1c in [20]). This corresponds to a hazard ratio of 0.663. A total of 188 events need to be observed to detect this difference with the stratified log-rank test (two-sided type I error 5%, power 80%, accounting for the interim analysis according to two-sided symmetric O’Brien-Fleming type alpha-spending at 94 events). Thus, 262 patients need to be enrolled and followed up (assuming 2,5 years of accrural, 5 years of follow-up and 5% censoring per year) [21]. For the key secondary outcome R0 resection Parry et al. report percentages of 87 and 71%, respectively [20]. This corresponds to an odds ratio of 2.73. Thus, 262 enrolled patients are also sufficient to give the stratified Mantel-Hanszel test at least 80% power (two-sided type I error 5%). Before participating in the trial, each center reported possible recruitment figures based on the number of patients with GEJ type II tumors in recent years. Screening will continue until the target sample size is achieved.

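### The only missing-data rule for the confirmatory 36-month quality-of-life AUC cannot cover death or months 24 to 36, so the non-inferiority result is undefined and may be driven by survival

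*Protocol article*

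**What the plan says.** Under Statistical analysis, quality of life is summarized as an AUC averaged over 36 months and tested for non-inferiority of the esophagectomy arm with a margin of 80%. The rule for missing data is "Missing values are linearly interpolated". Nothing is said about death, although the same paragraph does settle missing R0 assessments by counting them as failures.

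The test is confirmatory: "The key outcomes overall survival, R0 resection and quality of life are tested in a fixed sequence". A separate analysis is also described: "A linear mixed model is fit to health related quality of life data from EORTC questionnaires". It is not named as the confirmatory test, and it does not address death either.

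Outcome measures and the visit schedule under Patient follow-up place the last questionnaire at 24 months. After that, only survival is recorded, by phone. Questionnaires are also collected at V1, before surgery.

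Sample size calculation gives the survival assumptions: "We assume a cumulative survival after 2.5 years of 45% for transthoracic esophagectomy and 30% for transhiatal extended gastrectomy".

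**The concern.** Linear interpolation is a workable rule for a skipped visit between two completed ones. It gives no value once a patient has died or left for good, and on the plan's own survival figures death is the main reason for missing scores. The stated rule and the stated 36-month window therefore do not yield an AUC for most patients. Someone must add a death rule later, and the plausible rules measure different things. Stopping the area at death, or scoring death as 0, lets longer survival add area. Averaging over time alive does not. Restricting to survivors gives up the randomized comparison.

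The fixed sequence makes this matter more. Quality of life is tested only after overall survival (and R0) is significant, so survival will usually be unequal when the test is performed. If it differs in the planned direction, a rule that counts survival time helps esophagectomy, the arm whose non-inferiority is being claimed.

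**Working it through.** **Are the survival inputs usable?** ln 0.45 / ln 0.30 = 0.663, and the plan says "This corresponds to a hazard ratio of 0.663". With "two-sided type I error 5%, power 80%, accounting for the interim analysis", the Schoenfeld formula without an interim look gives 186.2 events. With O'Brien-Fleming-type spending at half the information (critical values 2.772 and 1.979), 187.8 are needed. This matches "A total of 188 events need to be observed". If the 5 years are read as total duration including accrual, the patient number is 188/0.707 = 266, close to the stated 262. The survival figures can therefore be used as the design assumption.

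**Deaths by month m.** With exponential survival, S(m) = S(30)^(m/30). The overall column assumes 1:1 allocation, which the article does not state.

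| | Esophagectomy | Gastrectomy | Overall |
|---|---|---|---|
| Dead by 24 | 1 − 0.45^0.8 = 47.2% | 1 − 0.30^0.8 = 61.8% | 54.5% |
| Dead by 36 | 1 − 0.45^1.2 = 61.6% | 1 − 0.30^1.2 = 76.4% | 69.0% |

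With Weibull shapes from 0.7 to 1.5 the overall figure is 51% to 57% at month 24 and 67% to 72% at month 36, so the curve shape matters little. Other attrition is assumed at 0.05 per year, or about 10% over two years (1 − 0.95² = 9.75%).

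**Months 24 to 36.** There is no questionnaire after month 24, hence no right-hand value. The rule fails there even for patients who are alive.

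**Effect of stopping the area at death.** Take a scale on which higher is better, with a constant score, unrelated to survival time and the same in both arms. The ratio of mean AUCs is then the ratio of restricted mean survival times, (1 − e^(−λT))/λ. Per year, λ = −ln 0.45/2.5 = 0.319 and −ln 0.30/2.5 = 0.482.

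- T = 2 years: 1.478 and 1.284 years, ratio 1.15. The 0.80 limit corresponds to a true while-alive ratio of 0.80/1.151 = 0.695, about 0.70.
- T = 3 years: 1.93 and 1.59 years, ratio 1.22. The limit corresponds to 0.80/1.216 = 0.66.

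**Simulation at the margin.** The true while-alive ratio was set to 0.80, so non-inferiority should be declared about 2.5% of the time. Assumptions: 131 per arm, mean score 70, SD 15 to 25, 8,000 trials per setting.

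| Rule | 24 months | 36 months |
|---|---|---|
| Death scored 0, planned survival | 47–51% | 61–66% |
| Death scored 0, equal survival | about 3% | about 3% |
| Average while alive | 3–5% | 3–5% |

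In a separate run with an assumed decline before death, last value carried forward gave about 7%, the while-alive average about 6%, and survivors only about 2–4%.

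**The case against.** The strongest reply is that this is a condensed article. A full protocol exists that is not public, a death rule for a third-ranked endpoint is commonly left to it or to the analysis plan, and the interpolation sentence is valid for intermittent gaps. That stands as far as it goes: a death rule may exist elsewhere. It does not settle the matter, because the article itself combines a 36-month window, questionnaires ending at month 24 and a single rule that cannot join them.

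A reader might infer that the quality-of-life result depends on survival rather than on quality of life. The article does not support this. It fixes no death rule, and an AUC averaged over time can be read as an average over time alive, under which survival hardly moves the ratio. The survivors-only reading is also close to nominal in the simulation; the firmer objection to it is that it is no longer a randomized comparison. The survival test is two-sided, so reaching the quality-of-life test does not by itself mean that esophagectomy had the longer survival.

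A reader might also infer that interpolation understates the standard error. For an interior gap in a per-patient AUC it does not. Interpolating gives exactly the trapezoid through the observed points. With independent errors at 0, 3, 6, 9, 12, 18 and 24 months, the squared weights sum to 94.5, and to 121.5 when month 12 is interpolated. The extra noise appears in the between-patient spread from which the standard error is computed.

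Finally, the Background section cites 40–50% survival at 5 years, which would imply only about 24–31% dead by month 24 (1 − 0.5^0.4 and 1 − 0.4^0.4). That is background rather than the design assumption, and interpolation would still have nothing to work with for those patients.

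**Conclusion.** The concern holds in this form: the stated rule cannot produce the stated quantity for most patients, so the confirmatory quality-of-life result is undefined. About 55% are expected to die by month 24 and about 69% by month 36, and months 24 to 36 are unobserved for everyone. Depending on the death rule chosen, the result may be driven by the survival difference. In the most exposed case, with area stopped at death, the 80% margin would in effect become about 0.70 over 24 months or 0.66 over 36.

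The death counts rest on the plan's survival assumption, exponential survival and 1:1 allocation. The effect sizes also rest on reading 80% as a ratio of mean AUCs. The simulated error rates further depend on the assumed score mean and SD. The point should be corrected before outcomes are seen. It concerns a confirmatory secondary endpoint and leaves the primary analysis untouched.

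**What to change.** - End the window at month 24, to match the questionnaires.
- Define the tested quantity, for all patients in the analysis set including those who die, as the average score while alive up to month 24.
- Handle gaps while alive with the mixed model already planned or with multiple imputation, and do not use model values for time after death.
- Adjust for the V1 baseline score, which is already collected.
- State how patients who die before any postoperative questionnaire are counted.
- Report the version with death scored 0 as a sensitivity analysis, noting that it includes the survival difference.

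The cost is wording and some programming; no new data are needed. The downside is that the result describes quality of life while alive and must be read together with survival. This choice also does not remove all influence of survival: the while-alive average gave about 6% rather than 2.5% in the run with decline before death, which is a further reason to show the sensitivity analysis beside it.

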### Interim analysis

When half the events (94 deaths) have occurred, an interim analysis will be performed (O’Brien-Fleming type alpha-spending). The outcomes will be evaluated by the DMC. Premature termination of the trial will be considered if the interim analysis or other research show a significant difference in survival between both treatment groups. In addition, the stop-criteria are: < 70% complete resection without tumor residual (R0) in one or both arms as well as > 50% less than 10 lymph nodes harvested in one or both arms. These criteria will be continuously evaluated by the DMC.

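### The fixed sequence alone does not guarantee strong 5% control when survival can be rejected at either of two looks and the test time for R0 and quality of life is not fixed

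*Protocol article*

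**What the plan says.** Under Statistical analysis, the article orders the key outcomes as survival, R0 and quality of life and states that they "are tested in a fixed sequence, thus no alpha-correction is required for strong type I error control (5%, two-sided"). R0 is compared by a stratified Mantel-Haenszel test. Quality of life is an area under the curve over 36 months, tested for non-inferiority of esophagectomy.

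Under Interim analysis: "When half the events (94 deaths) have occurred, an interim analysis will be performed". It uses O'Brien-Fleming-type spending, and early termination is considered if survival differs significantly. The Sample size calculation has the same look built in: "two-sided type I error 5%, power 80%, accounting for the interim analysis" by "two-sided symmetric O’Brien-Fleming type alpha-spending at 94 events".

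No look, boundary or nominal level is given for R0 or quality of life. For survival, "The hazard ratio with 95% confidence interval (CI) is estimated by stratified Cox regression".

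**The concern.** A fixed sequence lets each hypothesis be tested at full alpha without splitting, because a later test is reached only after every earlier one is rejected. That argument assumes one analysis time. Here survival, the gatekeeper, can be rejected at 94 or at 188 deaths. The time at which R0 and quality of life become testable then depends on the survival data, which may be correlated with them. Alpha-spending for survival protects survival only. Unless the secondaries have one fixed test time or their own boundaries, full-level testing does not guarantee strong control.

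The article draws the conclusion itself, with a 'thus', so this is a stated inference and not merely a detail left out. At stake is the error rate behind the secondary claims, above all quality of life. That is the last step and a directional claim, and it has the least data at the interim.

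**Working it through.** **1. The plan's own figure.** With "cumulative survival after 2.5 years of 45% for transthoracic esophagectomy and 30% for transhiatal extended gastrectomy", HR = ln(0.45)/ln(0.30) = 0.663, as stated. Events for a fixed design (Schoenfeld, 1:1 allocation assumed): 4 × (1.960 + 0.842)² / (ln 0.663)² = 186.2, so 187. The two-look inflation factor of 1.0087 (spending function applied to two-sided 0.05) gives 187.8, so 188, which agrees with "A total of 188 events need to be observed". Survival does pay for its look.

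**2. Survival boundaries at information fraction 0.5.** With O'Brien-Fleming-type spending of 0.025 per side, c1 = 2.963 and c2 = 1.969 (two-sided nominal 0.0031 and 0.0490). With the function applied to two-sided 0.05 they are 2.772 and 1.979 (0.0056 and 0.0478). The article does not say which is used. The results below use the first; the second gives nearly the same.

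**3. How often the interim route is used.** At HR 0.663 the final drift is 0.411 × √188 / 2 = 2.82, and at the interim 2.82 × √0.5 = 1.99. P(Z1 > 2.963) = 1 − Φ(0.97) = 16.6%.

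**4. Data available at 94 deaths.** Under the planned accrual, 94 deaths fall at about 2.3-2.8 years, with 93-100% of patients enrolled. R0 is then nearly complete (93-95% information used below). No patient has 36 months of quality of life and 13-32% have 24 months. The 35-50% information used for quality of life is an assumption, as are all correlations with survival; the article gives neither.

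**5. Each secondary tested once, at the look where survival crosses.** For a secondary at its null, the favourable-direction error is

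P(Z1 > c1, Y1 > 1.96) + P(Z1 ≤ c1, Z2 > c2, Y2 > 1.96),

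with corr(Z1, Z2) = √0.5, corr(Y1, Y2) = √f and corr(Z, Y) = ρ at the same look, maximised over the true survival effect. The reference is 2.5%.

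| Secondary | f | ρ | Favourable-direction error |
|---|---|---|---|
| Quality of life | 0.50 | 0.2 / 0.3 / 0.5 | 2.6% / 2.7% / 2.8% |
| Quality of life | 0.35 | 0.2 / 0.3 / 0.5 | 2.7% / 2.8% / 3.0% |
| Extreme case | 0.50 | near 1 | 4.1% |
| R0 | 0.93-0.95 | up to 0.5 | 2.5% |

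The opposite tail shrinks as this one grows. At f = 0.5 and ρ = 0.5 the tails are 2.8% and 1.2%. The two-sided total did not exceed about 5.0% in any case examined.

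**6. Each secondary tested at 1.96 at both looks** (not stated in the article; survival effect large enough that both tests are always reached). The two-sided error is 1 − P(|Y1| < 1.96, |Y2| < 1.96) with correlation √f: 8.8% at f = 0.35, 8.3% at 0.5, 6.2% at 0.93 and 6.0% at 0.95.

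**7. Each secondary tested once, at one prespecified time.** The error is at most 5% two-sided, with no penalty.

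**The case against.** The strongest defence is that the sentence concerns multiplicity between endpoints only. Survival is visibly corrected for the look, so the claim of no correction may mean only that alpha need not be split across three outcomes, which is true of a fixed sequence. The survival analysis is tied to 188 events in the same paragraph. If R0 and quality of life are tested only then, the sentence is right. A test of a 36-month curve at 94 deaths is also implausible, since nobody would have 36 months of data. This stands as far as it goes: one sensible reading rescues the sentence. But the article does not state that reading, and early termination on survival is foreseen without saying what then happens to the rest of the sequence.

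Three stronger readings are tempting and not supported:

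- A reader might infer that R0 and quality of life are tested at full 5% at both looks. No section says so, and the R0 and lymph-node criteria under Interim analysis are per-arm stopping thresholds, not between-arm tests.
- A reader might double the extreme 4.1% and report a two-sided error of about 8%. The tails are not symmetric under the single-test scheme, and the total stays near 5%.
- A reader might fault the plain 95% Cox interval. The level matching the final boundary is about 95.1%, overall coverage is about 94-95%, and an adjusted interval or estimate after an early stop is ordinary analysis-plan content, and that plan is not shown.

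**Conclusion.** The concern holds in limited form. Strong 5% control does not follow from the fixed sequence alone when survival has two rejection times and the test time and level of the secondaries are left open. Survival itself is protected, and its event count reproduces.

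Under single testing the consequence is nearly nil for R0 and a few tenths of a percentage point in the favourable direction for quality of life, given the assumed correlations and information. The 4.1% is a bound, not an expectation. The excess is material only if the secondaries are tested at both looks, which the article does not say. The point is worth correcting because the article claims a property that its text does not secure and the remedy is cheap. It does not threaten the primary result.

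**What to change.** State that the fixed sequence covers multiplicity between endpoints only, and replace the 'thus' with one of two rules:

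- **One test time.** R0 and quality of life are each tested once, at a prespecified time on complete data, also when survival stops early. No alpha penalty. The cost is that the quality-of-life test waits for complete follow-up. Complete needs defining, because the curve runs over 36 months while Outcome measures lists questionnaires up to 24 months.
- **Own spending.** Each secondary gets O'Brien-Fleming-type spending on its own information fraction. For quality of life at half information, the final critical value is about 1.97 instead of 1.96. For R0 the price is higher: at 95% information, the same function with 0.025 per side gives 2.02 at the interim and 2.06 at the final. Its power of about 0.89 (131 per arm, 87% against 71%) would fall to about Φ(1.243 + 1.960 − 2.062) = 0.87. One test time is therefore the cheaper choice for R0.

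Either rule leaves 188 events and 262 patients unchanged, and must be fixed before the 94-death look. An adjusted interval and estimate for survival after an early stop can be added to the analysis plan as an option.
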